**Study Design and Study Population**

A combination of two UK databases offers an excellent opportunity to study the clinical effects of interventions for obesity; the UK General Practice Research Database (GPRD) and QRESEARCH. In combination the GPRD and QRESEARCH contain information from >1100 UK general practices, and have current and historical data for >20 million patients. Continuous patient records include details of all consultations, diagnoses, prescribed medicines and basic demographic data. Patients are representative of the England & Wales population in terms of age, sex and geographical distribution [refs]. Data quality is subject to rigorous checks and audits and >500 peer reviewed studies have been published using GPRD or QRESEARCH data including studies investigating unintended effects of medication (GPRD, 2010; QRESEARCH, 2010). GPRD and QRESEARCH draw information from mutually exclusive practices and are therefore fully complementary.

*3.1 Study Design - Patient population, exposures of interest, inclusion/exclusion criteria*

The cohorts will comprise obese patients registered in the GPRD and QRESEARCH:

- Eligible patients will be those aged 18+ years with at least 12 months research standard registration time in the GPRD or QRESEARCH AND with one of the following exposures recorded by the study start:
  - A record of bariatric surgery with at least 12 months prior registration to ensure incident status (specific type of bariatric surgery used will be determined using data recorded in patient records); OR
  - A first prescription for orlistat with at least 12 months prior registration to ensure incident usage; OR:
  - A record of BMI>30 with neither bariatric surgery nor a prescription for orlistat – these patients will act as the **comparison group**
- The date of surgery or first orlistat prescription will be termed the index date. Each patient with surgery or orlistat will be matched with up to 5 obese patients without a record of these treatments, on age (within 5 years), sex and practice with at least 12 months research standard registration prior to the relevant index date.
- Patients will be followed until the earliest of; an outcome of interest, death, transfer out of the practice or last data collection date.

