**Statistical Analysis and Covariates**

*Baseline Comparisons*

We will use baseline data to compare the background characteristics of patients receiving surgical and pharmacological interventions for obesity with those receiving no intervention. This will give a broad picture of how these interventions are being targeted in the UK as a whole. Odds ratios and 95% confidence intervals will allow us to determine statistically and clinically relevant differences, using patients with no intervention as the baseline group. As a subgroup analysis, differences in the targeting of specific forms of bariatric surgery will also be determined. **Covariates** to be assessed will include age, sex, weight, BMI, smoking status, alcohol consumption and a range of co-morbidities such as coronary heart disease, hypertension and diabetes.

*Cohort analysis*

We will compare outcomes between patients receiving surgical and pharmacological interventions for obesity with those receiving no intervention. It is anticipated that these three groups of patients will differ in fundamental ways related to health outcomes that could represent important bias and confounding in this study. For this reason we will calculate propensity scores for each patient, capturing their likelihood to receive either surgery or a prescribed anti-obesity therapy. Using the propensity scores we will ensure comparisons are only made between patients with similar background characteristics (Sturmer et al, 2010). Cox proportional hazard regression will be used to conduct time to event analyses for death, diabetes, cardiovascular disease, fractures and liver disease, adjusting for the propensity score. Patients with no intervention will form the baseline group.

In addition, anonymised, linked Hospital Episode Statistic (HES) data are available for patients in the GPRD and will allow us to look in detail at hospital records for patients who undergo bariatric surgery (e.g. type of surgery, any complication that arise).

Patients who receive orlistat and later have surgery will move from one exposure group to the other, according to current treatment. We anticipate that very few patients will receive orlistat following surgery and any patients who appear to do so will be excluded from the analysis.

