For exposure to orlistat, follow up time will be censored 3 months after the date when prescribing information indicates treatment was stopped. This period allows for a degree of medication stockpiling and a treatment washout period. Similarly, follow up time for controls matched to orlistat recipients will be censored at the same date ensuring similar follow up in comparison groups.

Sensitivity analyses will stratify orlistat exposure on dose and duration using recorded prescribing information to estimate daily dose and duration of treatment.

Where possible, we will calculate number needed to treat (NNT) or number needed to harm (NNH) for clinical outcomes where a treatment effect is seen.

Linear regression will be used to compare changes in weight and BMI between surgical or pharmacological interventions and no intervention, adjusting for the propensity score. Changes will be calculated annually.

Similarly, a paired t-test will be used within each treatment group to determine changes in weight and BMI from baseline (pre-intervention). Changes will be calculated annually.

Absolute rates will also be determined for post-operative complications (post-operative haemorrhage, post-operative infection, ITU admission, re-admission to hospital and re-operation). Cox regression will be used to compare the hazard for each event between different types of bariatric surgery.

Initially the analysis will be done separately for QRESEARCH and GPRD data. It is anticipated the results will be very similar since the two datasets represent different samples of the same underlying population. Assuming the results are similar, data will be pooled, and a single analysis will be done, which will increase precision.

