**Limitations**

As mentioned above, it is likely that patients receiving surgery, pharmacological treatment or no intervention are likely to differ substantially. We will attempt to account for this by using propensity score matching, though we acknowledge that this may have an impact on power if few matches are available. Until the data are available we cannot predict the extent of this limitation.

Some patients may pay for their own surgical treatment abroad, which may not be instantly recorded by their GP, or in extreme cases may not be recorded at all. This could lead to a misclassification of exposure in the non-treatment group, though it is anticipated this will only affect a minority of this group.

Similarly orlistat is available over the counter and such use will not be well captured in primary care data. We will therefore conduct a sensitivity analysis of the effects of orlistat, censoring at the time the license first allowed over the counter sales (early 2009)

Data are likely to be missing for a small number of patients on some variables (e.g. smoking, alcohol consumption and BMI). For smoking and alcohol, missing values will be treated as a separate stratum during the construction of the propensity score. For BMI, we anticipate mostly complete recording as it is fundamental to the care of this patient group. However, in rare cases of missing post-index BMI measures, these patients will be excluded from the analysis for changes in BMI.

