**Amendment**

A number of amendments to this protocol are now sought:

1. Due to funding constraints, it will not be possible to access QRESEARCH data and the study will be restricted to CPRD data only. We do not anticipate major changes to the feasibility of the study, as the current number of patients in the CPRD with bariatric surgery is now >3,000.
2. Following initial data processing it became apparent that matches for bariatric surgery patients, drawn from the population of patients with a BMI >30 were very dissimilar from the surgery patients, mainly because the surgery group tended to have a much higher BMI. Since the guidelines for surgery include a requirement of BMI >=40 in most instances, we propose matches to be drawn from a pool of patients with any measure of BMI >=40 during their registration.
3. For the analysis of weight loss, we intend to measure the effects to a maximum of three years post-intervention, largely driven by the amount of follow up available for surgery patients
4. Following statistical advice from [name], it was decided that mixed effects linear regression should be used to assess changes in weight and BMI over time within each group. We anticipate a non-uniform rate of change over follow up and will model this using splines. The Akaike Information Criterion (AIC) will be used to determine optimal spline knot points. From the final model, weight/BMI and 95% confidence intervals for the study population will be estimated. The rate of change in weight or BMI and 95% confidence intervals will be calculated for each spline component.
5. For all other outcomes, orlistat patients will be censored at the end of follow up, analogous to an intention to treat type analysis, so the long term consequences of the decision to start a course of treatment with orlistat can be measured, regardless of subsequent treatment. As a sensitivity analysis, follow up will be censored at the estimated date treatment was stopped, based on prescribing records.
6. Subgroup analyses according to underlying diabetes and cardiovascular disease status will be carried out, in line with NICE recommendations for research on treatments for obesity. Additionally, where numbers permit, analyses of bariatric surgery patients will be stratified by surgery type.
7. As a clarification, patients who have bariatric surgery and later receive orlistat will be excluded from orlistat analyses only.

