  2. determine the relative risk of myocardial infarction in high­risk patients (i.e with cardiovascular risk factors) prescribed sibutramine or orlistat
  3. determine time to all­cause mortality in patients prescribed sibutramine or orlistat

1. Analysis plan

Initially, basic descriptive analyses of event rates will be conducted in each treatment group. Cox proportional hazard models will be used to investigate univariable and multivariable hazard ratios for the outcomes. Adjustment will be made for potential confounders (covariates to be assessed will include age, sex, weight, BMI, smoking status, alcohol consumption and a range of co-morbidities such as coronary heart disease, hypertension and diabetes). Following traditional regression analysis, propensity scores will be calculated to further explore possible prescribing biases and confounding, based on patient status with respect to the covariates listed above, and their orlistat/sibutramine exposure status. Our primary intention is to match sibutramine and orlistat patients with similar propensity scores, excluding any patients with scores in non-overlapping regions of the score distribution. Cox proportional hazards models will then be used to calculate Hazard Ratios for each outcome. Sensitivity analyses will also be used to estimate how large an effect an unknown confounder would need to have to eliminate or bring about any observed effect. We will also determine whether any effect is modified by age, sex, and area level social deprivation.

The cohort of obese patients already extracted contains over 27,000 patients prescribed sibutramine and 90,000 patients prescribed orlistat. Assuming a baseline 7% annual event rate (a two sided type I error rate of 0.05, and power set at 90%) to detect a 10% difference in hazard ratio between orlistat and sibutramine would require a sample size of 19,000 patients prescribed sibutramine and 58,000 patients prescribed orlistat. Assuming orlistat is not associated with an increased risk of vascular events, we estimate we have adequate power to detect an increased risk of MI, similar to the increased risk of MI and stroke detected in the SCOUT trial.

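### The between-group regression of weight and BMI change adjusts for baseline only through an unlisted propensity score; adding the baseline value directly is a free safeguard

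*Protocol*

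**What the plan says.** **Between-group analysis.** The Protocol, Statistical Analysis and Covariates, states: "Linear regression will be used to compare changes in weight and BMI between surgical or pharmacological interventions and no intervention, adjusting for the propensity score". This is done year by year. No other adjustment term is named.

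**The score.** The same section says "we will calculate propensity scores for each patient, capturing their likelihood to receive either surgery or a prescribed anti-obesity therapy". The covariates "to be assessed will include age, sex, weight, BMI, smoking status, alcohol consumption and a range of co-morbidities", but that list stands under Baseline Comparisons and is not said to define the score. Limitations comes close to doing so for smoking and alcohol, and then turns to BMI: "missing values will be treated as a separate stratum during the construction of the propensity score. For BMI, we anticipate mostly complete recording". Only for sibutramine against orlistat (Amendment, item 9) is the score expressly "based on patient status with respect to the covariates listed above", a list that includes weight and BMI.

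**Matching.** Comparators are matched "on age (within 5 years), sex and practice" (Study Design and Study Population). Amendment item 2 reports that the surgery matches were very dissimilar, "mainly because the surgery group tended to have a much higher BMI". In response, "we propose matches to be drawn from a pool of patients with any measure of BMI >=40 during their registration".

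**Later change of model.** Amendment item 4 introduces mixed effects regression with splines to describe weight and BMI within each group. It mentions neither a between-group contrast, nor the score, nor baseline. Specific Aims still calls for changes to be compared between groups, and item 8 gives weight and BMI one of the two planned papers.

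**The concern.** Baseline weight or BMI is a component of a change score and usually predicts it, because high starting values tend to fall back. It is also the variable on which the protocol itself found surgery patients and their matches most different. The quoted sentence leaves all the work on baseline to the propensity score.

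Whether that is enough depends on three things the protocol does not settle for this comparison: whether weight and BMI are in the score, whether their form in it is right, and whether there is one score per treatment or a single score for either. If any of these goes wrong, a heavier treated group would be expected to lose more even without treatment, and that part would be credited to the treatment.

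**Working it through.** The protocol gives no SD, correlation, power or sample size for weight or BMI, so there is no stated figure to reproduce. The inputs below marked as assumed are not from the protocol.

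**1. Precision.** Assume equal SDs (σ) at baseline and follow-up, with correlation ρ.
- Variance of unadjusted change: 2σ²(1 − ρ).
- Residual variance after adjusting for baseline: σ²(1 − ρ²).
- Ratio: (1 − ρ²) / [2(1 − ρ)] = (1 + ρ)/2. The SE ratio is its square root.

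| ρ (assumed) | variance ratio | SE ratio | SE saved |
|---|---|---|---|
| 0.5 | 0.75 | 0.866 | 13% |
| 0.8 | 0.90 | 0.949 | 5% |
| 0.9 | 0.95 | 0.975 | 3% |
| 0.95 | 0.975 | 0.987 | 1% |

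This compares with unadjusted change. A score that contains BMI already captures part of the gain. In the simulation in step 3, adding baseline BMI to such a score left the SE at 0.115 in one setting and moved it from 0.117 to 0.115 in the other.

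**2. What a residual imbalance would do.** Under the same assumptions the slope of untreated change on baseline is −(1 − ρ), that is −0.2 at ρ = 0.8 and −0.1 at ρ = 0.9. Each 10 kg of baseline difference that remains after adjustment shifts expected untreated change by 10 × 0.1 = 1 kg to 10 × 0.2 = 2 kg.

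**3. Does the score remove the imbalance?** Illustrative simulation, all inputs assumed: 6,000 patients, 60 repetitions, BMI SD of 5 units, raw imbalance about 0.87 SD, residual SD 3, true effect −10, slope of change on baseline BMI −0.1 or −0.3 per unit.

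| Score | imbalance left (SD) | estimate, score only (slope −0.1 / −0.3) | score plus baseline BMI |
|---|---|---|---|
| BMI in score, correct form | about 0.00 | −10.00 / −9.99 | −10.00 / −9.99 |
| BMI not in score | about 0.88 | −10.44 / −11.29 | −10.00 / −9.99 |

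Hand check of the second row: 0.1 × 5 × 0.88 = 0.44 and 0.3 × 5 × 0.88 = 1.32, against simulated biases of 0.44 and 1.29.

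**4. Intermediate cases.**
- *Single score for either treatment.* The sentence on the score can be read this way. Sample Size/Power Calculation gives about 80,000 orlistat and 2,000 surgery patients, a ratio of 40 to 1, so such a score would mostly describe orlistat prescribing. With BMI assumed strongly related to surgery and weakly to orlistat, one illustration left 0.58 of a 0.95 SD imbalance. With BMI SD 5 this is 0.58 × 5 × 0.1 = 0.29 to 0.58 × 5 × 0.3 = 0.87 units. The result depends heavily on the assumed coefficients: when BMI also predicts orlistat clearly, almost nothing remains.
- *Surgery-specific score lacking a curvature term in BMI.* One illustration left about 0.3 SD in the opposite direction, or 0.3 × 5 × 0.1 = 0.15 to 0.3 × 5 × 0.3 = 0.45 units.

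**5. Does the new pool settle it?** No. A BMI of 40 or more at any time in registration need not be the value at the index date, the rule sets a floor and does not match above it, and the item concerns surgery matches only.

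**The case against.** The strongest reply is that baseline is already adjusted for. Weight and BMI are on the covariate list, the score is introduced to deal with group differences, and Limitations discusses BMI next to the construction of the score. The natural reading is that BMI is in it. Given a correct score, baseline BMI has the same distribution in both groups, and differences in starting weight between individuals with the same score are spread, not confounding. This stands, and step 3 bears it out.

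A reader might therefore infer too much in two ways. One is that the analysis ignores baseline weight and BMI and so keeps the imbalance. The protocol does not support this: the score probably contains BMI, the reported difference came from the pool with BMI above 30 that has since been replaced for surgery matches, and the plan also intends to compare only similar patients and mentions propensity score matching. The other is to count as bias the larger loss in kilograms that heavier surgery patients would have if loss is proportional to weight. For an effect in the treated group, that is part of the effect.

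It can also be said that amendment item 4 replaced the quoted regression. This is not clear. The item is confined to within-group description, which fits the earlier paired t-test, while Specific Aims keeps the between-group comparison. If item 4 was meant to replace both, no between-group adjustment for weight or BMI is stated at all. A mixed model that takes baseline as part of the outcome, with a free starting level in each group, would not by itself adjust for the difference.

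**Conclusion.** The point holds as a free improvement, not as a demonstrated bias. Baseline weight and BMI enter the between-group comparison only indirectly, through a score whose variables are not listed for it, and the new comparator pool need not equalise BMI at the index date.

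If the score contains BMI in the right form, the loss is a small amount of precision: about 1-5% in SE at an assumed correlation of 0.8-0.95, and less where the score already explains part of the change. If the score omits BMI, has the wrong form or is pooled over both treatments, residual imbalance may pass into the treatment difference. The largest illustrated bias is 1.3 on a true effect of 10, with BMI omitted altogether. Every size given rests on assumed SDs, slopes and correlations. What does not depend on them is that the direct baseline term costs essentially nothing when the score is right and protects when it is not.

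**What to change.** - In Statistical Analysis and Covariates, change the adjustment to: *adjusting for the propensity score and for baseline weight (or BMI) as a continuous covariate*, using the baseline value of the outcome analysed.
- Use the same baseline adjustment in any between-group mixed model under amendment item 4.
- State that the between-group comparison of weight and BMI change still applies after item 4, and by which model.
- It would help to list the score's variables for this comparison and to say whether there is one score per treatment.

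A baseline-by-group term and reporting of percentage change are optional.

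The cost is a few lines of wording. No new data are needed, and no patient is lost, because a change from baseline cannot be calculated without the baseline value.

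### The Cox comparison of complications between types of bariatric surgery states no confounder adjustment, and the protocol's propensity score is not designed to balance operation types

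*Protocol*

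**What the plan says.** All of the following is in the Protocol, Statistical Analysis and Covariates, unless stated otherwise.

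- **The analysis at issue.** "Absolute rates will also be determined for post-operative complications (post-operative haemorrhage, post-operative infection, ITU admission, re-admission to hospital and re-operation") is followed directly by "Cox regression will be used to compare the hazard for each event between different types of bariatric surgery". Nothing is said about adjustment.
- **The propensity score.** It is described as "capturing their likelihood to receive either surgery or a prescribed anti-obesity therapy". The reason given for it is that "It is anticipated that these three groups of patients will differ in fundamental ways related to health outcomes", where the three groups are surgery, drug treatment and no intervention.
- **Use of the score.** "Using the propensity scores we will ensure comparisons are only made between patients with similar background characteristics". Cox models then serve "time to event analyses for death, diabetes, cardiovascular disease, fractures and liver disease, adjusting for the propensity score", and "Patients with no intervention will form the baseline group".
- **Operation types at baseline.** As a subgroup analysis of baseline characteristics, "differences in the targeting of specific forms of bariatric surgery will also be determined".
- **Other adjusted models.** The linear regression for weight and BMI against no intervention is also adjusted for the propensity score. The sibutramine versus orlistat comparison (Amendment, item 9) has multivariable adjustment and a propensity score of its own.
- **Later changes.** Amendment item 6 stratifies analyses of surgery patients by type of surgery where numbers allow. The amendment of 21 May 2015 stops using HES for myocardial infarction only. Neither adds adjustment to the complications model.

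**The concern.** Patients are not randomised to an operation. If those who receive one operation are heavier, have more comorbidity or were operated on in a different period, a crude hazard ratio for haemorrhage, infection, ITU admission, re-admission or re-operation mixes those differences with the effect of the operation.

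The protocol deals with this problem explicitly in its other between-group comparisons but not here, and the one score that an analyst might carry over was built for a different contrast. An analyst who follows the text would fit either a crude model or a model adjusted for a score that does not describe the choice of operation. The resulting hazard ratios could be taken as a safety comparison of operations. The Limitations section would not caution against this, because it discusses differences among surgery, drug treatment and no intervention only.

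**Working it through.** The protocol gives no effect size, event rate, type I error or power for this comparison, so there is no figure to reproduce. The check is mainly a reading of the text. The calculations show what could happen under assumed inputs.

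**1. Does any stated adjustment reach this model?**

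| Comparison | Stated adjustment | Reference group |
|---|---|---|
| Death, diabetes, cardiovascular disease, fractures, liver disease (Cox) | Propensity score | No intervention |
| Weight and BMI (linear regression) | Propensity score | No intervention |
| Sibutramine v orlistat (Cox, Amendment item 9) | Covariates, then its own score | Other drug |
| Complications by type of surgery (Cox) | None stated | Another operation |

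The general statement about comparing only similar patients refers to the score defined immediately before it, for the three treatment groups. A comparison within surgery patients has no untreated reference group, and complications are not among the outcomes listed for the adjusted Cox models.

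**2. How far could one unbalanced factor move the crude ratio?** Take a true ratio of 1 and a binary risk factor with risk ratio RR, present in proportions pA and pB of two operation groups. Then

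apparent ratio = (1 + pB(RR − 1)) / (1 + pA(RR − 1)).

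All inputs are assumed:

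| pA | pB | RR 1.5 | RR 2 | RR 3 |
|---|---|---|---|---|
| 30% | 40% | 1.04 | 1.08 | 1.13 |
| 30% | 50% | 1.09 | 1.15 | 1.25 |
| 20% | 50% | 1.14 | 1.25 | 1.43 |

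For example, at 20% v 50% and RR 2: (1 + 0.5)/(1 + 0.2) = 1.5/1.2 = 1.25. With no imbalance the ratio is 1.00.

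**3. How often would such a ratio be declared significant?** With D events split 1:1, power ≈ Φ(ln(HR)·√D/2 − 1.96). The Amendment (item 1) gives more than 3,000 surgery patients; 3,000 is used here. The complication rates and the even split are assumed.

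- 10% rate, D = 300: HR 1.25 gives Φ(0.223 × 8.66 − 1.96) = 49%; HR 1.43 gives 87%.
- 3% rate, D = 90: HR 1.25 gives 18%; HR 1.43 gives 40%.

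The nominal rate is 5%. These percentages are generous, because the Outcomes section says that HES data, from which the complications are taken, cover a large proportion of the cohort, not all of it.

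**4. Would the existing score help if it were carried over?** One simulated population had two confounders, a true hazard ratio of 1 between operations and 39,885 surgery patients. The score modelled surgery versus none.

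| Operation type depends on | Crude | Adjusted for surgery score | Adjusted for covariates |
|---|---|---|---|
| One covariate only | 1.41 | 1.26 | 1.06 |
| Both, in opposite directions | 0.89 | 0.81 | 0.99 |
| Same combination as surgery itself | 1.44 | 1.03 | 1.03 |

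The score removed nearly all the bias only in the third case, left much of it in the first, and moved the estimate further from 1 in the second. These are single runs and carry some sampling error.

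**The case against.** The strongest objection is that silence is not error. The protocol names a method and a contrast and never calls the model crude or univariable. A covariate list for a secondary, surgery-only model could sit in a statistical analysis plan, and none is among the documents. Repeating the phrase about the propensity score would also have been inapt, because that score was built for other contrasts. This has weight: a reader might infer that the plan commits to an unadjusted analysis, and the text does not say so. What remains is that the protocol has its own section on analysis and covariates, states adjustment for the other between-group models, and offers only a score that does not fit this contrast.

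Three further limits are fair.

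- A reader might infer that the protocol expects different operations to be targeted at different patients. It does not say that. It says that such differences will be determined. The stated expectation of fundamental differences concerns surgery, drug treatment and no intervention.
- A reader might extend the point to Amendment item 6. That item splits surgery analyses by type and specifies no contrast of one operation with another, so the point does not apply there.
- The comparison is peripheral. The Objectives concern surgery against drug treatment and against no treatment, although the Specific Aims do list complications among the outcomes to be compared between groups.

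**Conclusion.** The point holds in a limited form. No confounder adjustment is stated for the comparison between operations, and the defined score is not designed to balance operation types. It is too strong to say that the score could never help, since in one of the three simulated cases it did.

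The size and direction of any bias are unknown. The documents give no split by operation, no complication rates and no characteristics by operation type. The range of 1.04 to 1.43 rests wholly on assumed prevalences and risk ratios. It shows that moderate imbalance could produce a material apparent difference, not that it does so here. Nor do the documents support a prediction that readers will take selection for an effect of the operation; the text only leaves that open. This is a worthwhile correction to a secondary safety comparison and does not touch the main comparisons.

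**What to change.** In Statistical Analysis and Covariates, after the sentence on Cox regression between types of surgery, state that:

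- these models adjust for pre-operative covariates that the section already lists (age, sex, BMI, smoking and comorbidities such as coronary heart disease, hypertension and diabetes), plus calendar year of surgery;
- where events are few, they adjust instead for a separate propensity score for operation type, estimated among surgery patients only;
- crude absolute rates by operation type are reported alongside;
- comparisons with too few events for either approach are labelled descriptive.

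The cost is wording. The covariates are already planned, and the date of surgery is already held as the index date. The downside is limited information for rare complications. Counting one term each for age, sex, BMI, smoking, three comorbidities and year gives eight terms, and the illustrative 90 events would leave 90/8 ≈ 11 events per term before any term for operation type. Rarer complications may support only a score or a few covariates.
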